## **2.4 Description of and justification for the route of administration, dosage, dosage regimen and treatment period(s).**

### *Rationale For Study Design And Key Questions From Our Pilot Study:*

#### *2.4.1 Concomitant antigen responses:*

Other vaccine antigens co-administered with Pa-containing vaccines include diphtheria, tetanus, polio, Hepatitis B and *Haemophilus influenzae* type b (Hib). In the German study, attainment of Hib antibody responses indicating protection (>0.15ug/ml) was significantly lower after the first 3 doses (88% vs. 98%). Reduced Hib immunogenicity has been associated with DTPa-Hib combination vaccines, but has only emerged as a clinical problem in the UK prior to that country introducing a Hib booster. In Australia, a Hib booster has always been routine.

There was no significant difference in response to other antigens. In our pilot study, hepatitis B antibody levels were non-significantly lower in the birth Pa group, but all participants were above the accepted threshold for protection (>10mIU/L). This study will examine IgG responses to D, T, Hib and hepatitis B post primary immunisation.

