## 3.2 HYPOTHESES

1. IgG antibody responses to pertussis toxin (PT) and pertactin (PRN) in infants receiving monovalent acellular pertussis vaccine (Pa) at birth and routine vaccines at 6 weeks are significantly higher than in unvaccinated infants by 10 weeks of age, and remain higher at 6 and 8 months of age
2. Cell-mediated immune responses to PT and PRN at 10 weeks and 8 months of age in infants receiving monovalent acellular pertussis vaccine at birth and routine vaccines at 6 weeks do not differ significantly from those in infants with first doses at 6 weeks.
3. IgG antibody responses to **PT and PRN** at each time point in infants of mothers vaccinated with dTpa within the previous 5 years do not differ significantly from infants of unvaccinated mothers.
4. In infants receiving Pa at birth and routine vaccines at 6 weeks, the prevalence of antibody levels consistent with protection to **other vaccine antigens** is not significantly reduced
5. The frequency, duration and intensity of solicited symptoms in the 6 days following vaccination and unsolicited symptoms until the next vaccination visit (up to 8 months old) will not differ significantly between the infants receiving Pa vaccine at birth and controls.

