### 14.1 A description of the statistical methods to be employed, including timing of any planned interim analysis(es).

All serum antibody concentrations will be log transformed for statistical analysis as geometric mean concentrations (GMC). Where protective thresholds are well established, the proportions at or above the assay cut off – anti-diphtheria (0.1 IU/ml)\*, anti-tetanus (0.1 IU/ml) anti-Hib (PRP) (0.15 µg/ml) and hepatitis B surface antibody (10mIU/ml) – will be compared by vaccine group. Antibody to polio serotypes 1, 2 and 3 will be measured by microneutralisation assay and the lowest dilution tested at 1:8. Statistical analysis will include both comparisons of GMC (with 95% confidence intervals) as a continuous variable (t test) and categorical analysis of relevant Ab. Thresholds (chi square). Analysis will be performed with the assistance of the NHMRC Clinical Trials Centre, independent of the testing laboratory. *Note: \* this threshold is significantly above the known protective level of 0.01 IU/ml but is the lower limit of assay detection.*

The primary analysis will be a comparison in the susceptibility rate (no measurable PRN nor PT) between the two groups at week 10 (or last post-baseline observation carried forward) using a chi-square test. The applicability of more sophisticated analysis approaches that adjust for covariates (e.g. logistic regression) and model the repeated assessments of susceptibility over time Week 6, Week 10, Month 6, Month 8 will be investigated.

The other antibody threshold data collected at Month 8 will be analysed using same approaches as those outlined above for the Week 10 susceptibility data.

The log-transformed antibody concentrations will be analysed using a linear model with treatment group, site and maternal dTpa vaccine status as factors. The applicability of repeated measures analysis methods (e.g. mixed-model) will also be explored for the concentration data.

The analysis of safety data will be primarily descriptive in nature.

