### 14.2 The number of subjects planned to be enrolled.

#### 14.2.1 Antibody measures:

Lack of any measurable antibody to both PT and PRN is the best available indicator of susceptibility to severe pertussis. Accordingly, we have based sample size calculations on reduction in the proportion of susceptible infants as early as possible. If superiority of birth pertussis vaccine is defined as a reduction of 12% or more in the proportion of subjects

lacking antibody (no measurable PRN or PT) compared with controls at 10 weeks old, a sample size of 220 in each maternal arm will have 80% power to detect a reduction of this magnitude at a two-sided alpha level of 0.05. This is not altered by a differing prevalence of detectable pre-immunisation antibody among controls over the range of 65% to 75%. (Sample Power V2 [www.spss.com](http://www.spss.com)) This study will recruit 110 participants in each of the 4 arms, a total of 440 participants allowing for a 10% drop out rate.

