### **14.3 The level of significance to be used.**

Hypothesis tests and confidence intervals will be two-sided with alpha set to 5%.

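### Hypotheses 2 to 4 are supported by a non-significant difference and no margin is set, so a moderate loss of response could be read as no interference; hypothesis 5 has no matching analysis

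*Protocol*

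**What the plan says.** Section 3.2 of the protocol words hypotheses 2 to 5 in the same way:

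- Hypothesis 2 (cell-mediated responses to PT and PRN): responses after a birth dose "do not differ significantly from those in infants with first doses at 6 weeks".
- Hypothesis 3 (maternal dTpa): infant antibody responses "do not differ significantly from infants of unvaccinated mothers".
- Hypothesis 4 (other vaccine antigens): the prevalence of protective levels "is not significantly reduced".
- Hypothesis 5 (solicited and unsolicited symptoms): these "will not differ significantly between the infants receiving Pa vaccine at birth and controls".

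Section 14.1 compares antibody thresholds by chi-square test and geometric mean concentrations (GMCs) by t test with 95% confidence intervals. It also plans a linear model for log concentrations with treatment, site and maternal dTpa status. The Month 8 thresholds for the other antigens use the same approach as the primary comparison. On safety it says: "The analysis of safety data will be primarily descriptive in nature". Section 14.3 adds: "Hypothesis tests and confidence intervals will be two-sided with alpha set to 5" per cent.

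Section 14.2.1 sizes the trial for superiority on pertussis susceptibility alone: "a sample size of 220 in each maternal arm will have 80% power to detect a reduction of this magnitude". Section 14.2.2 sizes the cellular work to detect a difference in IL-5. No non-inferiority margin, equivalence band or tolerable loss is stated anywhere.

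Section 2.4.1 gives the reason for concern about other antigens. In a birth-dose study, attainment of the Hib threshold "was significantly lower after the first 3 doses (88% vs. 98" per cent).

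**The concern.** A difference test that fails to reject does not show that groups are alike. When the hypothesis itself is the absence of significance, dropout, missing sera and assay noise all push the result towards support, and nothing in the protocol limits how large a loss can go undetected.

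Secondary objectives 2 and 3 in section 4.2 (interactions with concurrent antigens, and adverse effects of early Pa) bear on whether a birth dose can be added without weakening responses to Hib, hepatitis B, diphtheria and tetanus. The background shows how this could happen: section 2.4.1 reports hepatitis B antibody as non-significantly lower in the pilot's birth-dose group. Under the wording of hypothesis 4, a result of that kind would count in its favour.

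Hypothesis 5 has a different problem. It is worded as a significance statement, but the safety analysis is mainly descriptive.

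**Working it through.** **1. The plan's own figure.** Inputs from 14.2.1: a 12-point reduction, 80% power, two-sided 0.05, 10% dropout. Detectable antibody in 65-75% of controls is read as 25-35% susceptible, and the 220 is read as per vaccine group.

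n = [1.96·√(2p̄(1−p̄)) + 0.8416·√(p₁q₁+p₂q₂)]² / d²

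For 30% vs 18%: p̄ = 0.24, and n = (1.96 × 0.6040 + 0.8416 × 0.5980)² / 0.12² = 2.846 / 0.0144 ≈ 198. Then 198 / 0.9 = 220, which matches. So 198 evaluable per group is the planning figure used below.

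**2. Hypothesis 4: chance of a non-significant result despite a real fall.** The protocol gives no expected Month 8 rates, so the rates are assumptions.

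P(non-significant) = 1 − Φ[(d − 1.96·SE₀)/SE₁], with SE₀ = √(2p̄(1−p̄)/n) and SE₁ = √((p₁q₁+p₂q₂)/n).

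Example, 95% to 90%, n = 198: SE₀ = 0.02647, SE₁ = 0.02635, (0.05 − 0.05188)/0.02635 = −0.07, so P = 1 − 0.47 = 0.53.

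| True fall | n = 198 | n = 220 |
|---|---|---|
| 98% to 95% | 0.63 | 0.60 |
| 98% to 93% | 0.33 | 0.28 |
| 95% to 90% | 0.53 | 0.49 |
| 90% to 85% | 0.68 | 0.65 |
| 98% to 88% (size of the cited Hib loss) | 0.024 | 0.014 |

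Exact binomial enumeration at n = 198 agrees: 0.63, 0.30 and 0.52 for the first three rows, and 0.012 for the last. With only 99 per group, 95% to 90% is non-significant with probability 0.735, so fewer data make support more likely.

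**3. Hypothesis 3.** The protocol gives no antibody SD. A log10 SD of 0.4 to 0.6 and 198 per maternal stratum (equal strata) are assumed.

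P(non-significant) = 1 − Φ[log10(r)/(SD·√(2/n)) − 1.96].

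For r = 1.25 and SD = 0.5: 0.0969/0.0503 − 1.96 = −0.03, so P = 0.51. Over the SD range, a true 1.25-fold difference is missed 33-64% of the time and a 1.5-fold difference 1-17%.

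**4. What a margin would do.** With no true difference, power = Φ(m/SE − 1.96), SE = √(2p(1−p)/198). The margins are illustrations.

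| Common rate | SE | 5 points | 7.5 points | 10 points |
|---|---|---|---|---|
| 95% | 0.0219 | 0.63 | 0.93 | >0.99 |
| 90% | 0.0302 | 0.38 | 0.70 | 0.91 |

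Exact enumeration with the score test behind the Miettinen-Nurminen interval gives about 0.89, not 0.93, for 7.5 points at 95%.

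The same exact calculation gives the chance of passing when there is a real fall (n = 198):

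| True fall | Chi-square non-significant | Lower limit above −10 | Lower limit above −7.5 |
|---|---|---|---|
| 98% to 95% | 0.63 | 0.90 | 0.56 |
| 98% to 93% | 0.30 | 0.56 | – |
| 95% to 90% | 0.52 | 0.43 | 0.14 |
| 98% to 88% | 0.012 | 0.021 | – |

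A 10-point margin is therefore more permissive than the present test when control rates are near 98%.

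**5. Hypothesis 5.** No calculation applies. Section 3.2 states a significance criterion, while 14.1 names no safety test and calls the analysis mainly descriptive.

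**The case against.** Several points on the other side stand.

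- **No decision rule is written down.** A reader might infer that the protocol declares a hypothesis confirmed whenever p exceeds 0.05. It does not say so. Section 3.2 lists hypotheses, and the secondary objectives in 4.2 are neutrally phrased. The problem follows from the wording combined with the planned tests.
- **The analysis is not limited to bare tests.** Section 14.1 also provides GMC confidence intervals, a linear model and possible logistic or mixed models. A loss in hepatitis B response could show in GMCs even if every infant were above the threshold. But no rule says how those intervals bear on the hypotheses.
- **Large losses would be seen.** A reader might infer that the cited Hib loss could slip through. At the planned size it would not, except about 1-2% of the time.
- **Hypothesis 5 is not exposed to a misread p-value.** It is tempting to include it in the same criticism, but no safety test is planned. Sections 5.1 and 5.5.2 also disclose that the open-label design limits assessment of irritability and crying. What remains is a mismatch in wording.
- **For IL-5, non-significance is not empty.** Section 14.2.2 plans 90% power for a difference above 0.25 in log IL-5. That is a detectable difference, not a margin, and it covers one cytokine.
- **An analysis plan could add margins.** It could, but it would then be testing a different statement from the one in the protocol.

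**Conclusion.** The point holds for hypotheses 2, 3 and 4: as worded, a non-significant difference supports them, and the planned tests and sample size put no limit on the loss that could go unnoticed. For hypothesis 4, at 198 per group, moderate falls of 3 to 5 points are non-significant roughly 30% to 68% of the time, depending on the assumed control rate (90-98%). The hypothesis 3 figures rest on assumed SDs and equal strata. Hypothesis 2 has the same form, but no size of risk is calculated for it here.

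For hypothesis 5 the finding is narrower: sections 3.2 and 14.1 do not match. The primary superiority comparison is unaffected. The documents do not support saying that a loss as large as the cited Hib one is likely to be missed, or that the protocol states an explicit rule equating p above 0.05 with no effect. This should be corrected, but it does not threaten the trial's main result.

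**What to change.** - **Hypothesis 4.** For each antigen, report the birth-minus-control difference in the proportion at or above threshold, with a two-sided 95% Miettinen-Nurminen interval. Conclude no interference only if the lower limit excludes a margin that the sponsor fixes and justifies before seeing data; otherwise report that it was not shown. The margin should be tighter than the 10-point Hib loss the protocol cites, because at 10 points a true fall from 98% to 95% would pass 90% of the time. At 7.5 points, power with no true difference is about 89-93% at 95% seroprotection and about 70% at 90%.
- **Hypotheses 2 and 3.** Report differences or GMC ratios with 95% confidence intervals as estimation, or against a band justified in advance. Do not infer no difference from p above 0.05. The protocol offers no basis for a particular band, so none is proposed here.
- **Hypothesis 5.** Drop the no-significant-difference wording and report risk differences with 95% confidence intervals, in line with 14.1.

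The cost is in wording and in justifying margins, and some no-interference claims become harder to make. No extra infants, blood or assays are needed.

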## 4 Study Objectives and Endpoints

### 4.1 Primary

To establish if earlier protection from severe disease due to *Bordetella pertussis*, as measured by PT and PRN antibody (Ab) and cell mediated immune (CMI) responses, is achieved by monovalent acellular pertussis vaccine (Pa) at birth *versus* vaccination schedules commencing at 6 weeks of age.

### 4.2 Secondary

1. To determine whether maternal receipt of adult-formulated acellular pertussis vaccine (dTpa) within the previous 5 years influences infant Ab or CMI responses.
2. To evaluate interactions with vaccine antigens given concurrently at birth (hepatitis B) or later
3. To evaluate adverse clinical or immunological effects from early use of Pa vaccine.

### 4.3 Measurement of antibody and CMI responses

Measurement of antibody by a reference laboratory with rigorous standardisation and evidence of reproducibility is essential. The GlaxoSmithKline (GSK) laboratories in Belgium have long experience with pertussis antibody assays, validated by the US Food and Drug Administration, for many clinical trials in infants from 2 months of age. To maximise comparability of the proposed trial with the previous pilot results and to ensure high assay standards, we have contracted with the GSK laboratory to undertake the assays for pertussis antigens, Diphtheria (D), Tetanus (T), hep B, pneumococcal serotypes (10 serotypes if volume of blood sample permits) and Hib. The expertise of this laboratory also enables measurement of antibody to the widest possible range of relevant vaccine antigens using minimal blood volumes. With respect to measurement of CMI, the laboratory of [name] and [name], ICHR, Perth has an international reputation and previous experience in pertussis-specific assays and will conduct these assays. In the pilot study, we demonstrated that the transport of viable samples for CMI assay to Perth was possible.

## 5 Study Design

### 5.1 Study type

The study will be stratified, randomised but not blinded. Lack of blinding limits the potential to examine non-specific adverse reactions, such as irritability and abnormal crying, but we judge a placebo not justified according to guidelines or the Declaration of Helsinki 1999. The trial will be registered with the Australian Clinical Trials Registry.

### 5.2 Stratification

This will be by maternal immunisation status / past history of pertussis infection before randomization in two groups:

**Stratum A** – maternal dTpa vaccine or history of maternal pertussis infection within last 5 years.

**Stratum B** – no previous maternal dTpa vaccine or dTpa vaccine > 5 years pre-delivery and no history of maternal pertussis infection during last five years.

A maternal history of Pertussis infection will be accepted as positive if the participant's mother reports that the diagnosis was made by blood test or throat swab and confirmation of diagnosis via blood test or throat swab is received by her healthcare provider.

NOTE: If a mother receives dTpa vaccine after delivery of child but before enrolment of infant then infant should be stratified into stratum B.

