### 5.3 Randomisation

Once written informed consent has been provided and eligibility has been confirmed, the participant will be issued with a unique participant number. The participant number will be used to identify the participant for the duration of the study. Neonates will be randomly assigned, in a 1:1 ratio to one of two groups (Table 2):

**Birth group** (early vaccination) Pa vaccine at birth, 6 weeks, 4 months and 6 months.

**Control group** (standard vaccination) usual vaccinations at 6 weeks, 4 months and 6 months.

[figure not shown]

Participants will be randomized using the central randomisation service at the NMHRC Clinical Trial Centre, Sydney, by automated interactive voice response system (IVRS) (available 24hrs). Investigators and study research staff will follow the voice prompts on the IVRS and complete the randomisation worksheet. Participants will be allocated to either the Pa vaccine at birth or No Pa vaccine given at birth groups via the IVRS.

Before randomisation, stratification into either the 'maternal dTpa vaccine prior to birth within 5 years' group / history of maternal pertussis infection < 5years **or** no maternal dTpa

vaccine < 5years / no history of maternal pertussis infection < 5years will be conducted according to maternal verbal report.

Subsequently attempts will be made to confirm maternal verbal report of receipt of dTpa vaccine or history of laboratory confirmed maternal infection by obtaining verification from the maternal healthcare provider. If no confirmation of mother having received dTpa vaccine within last 5 years (prior to enrolment) or history of laboratory confirmed maternal infection with pertussis is obtained, the mother/infant will be re-allocated to the no maternal dTpa vaccine group for the purpose of secondary analysis only.

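### The re-allocation rule in section 5.3 leaves mothers with confirmed pertussis but no dTpa on the exposed side of a secondary contrast that is stated to be about maternal dTpa

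*Protocol*

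**What the plan says.** Two places state the maternal question, and both name vaccine alone. Secondary objective 1 (Protocol section 4.2) reads: "To determine whether maternal receipt of adult-formulated acellular pertussis vaccine (dTpa) within the previous 5 years influences infant Ab or CMI responses". Hypothesis 3 (section 3.2) says that pertussis IgG responses "in infants of mothers vaccinated with dTpa within the previous 5 years do not differ significantly from infants of unvaccinated mothers". Neither mentions maternal infection.

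The groups are built differently. Section 5.2 defines Stratum A as "maternal dTpa vaccine or history of maternal pertussis infection within last 5 years" and Stratum B as "no previous maternal dTpa vaccine or dTpa vaccine > 5 years pre-delivery and no history of maternal pertussis infection during last five years".

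Section 5.3 stratifies on the mother's verbal report and then seeks verification from her healthcare provider. If neither recent dTpa nor a "history of laboratory confirmed maternal infection with pertussis is obtained", the pair is "re-allocated to the no maternal dTpa vaccine group for the purpose of secondary analysis only".

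Section 14.1 analyses log antibody concentrations with a "linear model with treatment group, site and maternal dTpa vaccine status as factors". It does not define that last factor or say that it equals the stratum.

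**The concern.** The group name and its membership rule disagree. The name refers to dTpa, but confirmed infection is enough to stay on the exposed side. This does not depend on poor records: it holds even if every history is fully verified.

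At stake is the reading of one secondary result. Hypothesis 3 predicts no significant difference. If infection-only mothers resemble mothers with neither exposure, including them pulls the contrast toward that prediction. If recent infection leaves more antibody than vaccine, part of an infection effect would be reported as a dTpa effect.

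A second, smaller inconsistency concerns the comparator. Hypothesis 3 calls these mothers unvaccinated, whereas Stratum B includes mothers given dTpa more than 5 years before delivery.

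**Working it through.** The plan states no sample size, power or expected difference for the maternal contrast, so there is no figure to reproduce. The check compares definitions and then gives an illustration.

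**Step 1: where each type of mother falls, all histories confirmed.**

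| Mother | Hypothesis 3 | Objective 1 | Sections 5.2 and 5.3 |
|---|---|---|---|
| dTpa within 5 years | exposed | exposed | exposed |
| No dTpa, pertussis within 5 years | unvaccinated, so comparator | no recent dTpa, so comparator | **exposed** |
| dTpa over 5 years ago, no recent pertussis | neither side | no recent dTpa, so comparator | comparator |
| No dTpa, no recent pertussis | comparator | comparator | comparator |

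The second row conflicts with both statements of the question. The third conflicts with the wording of Hypothesis 3 only.

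**Step 2: does the conflict reach the analysis?** The condition in section 5.3 is that neither exposure is confirmed. The other grammatical reading, moving a mother when either one is unconfirmed, would remove nearly everyone who does not have both, and cannot be meant. So a mother with confirmed infection and no dTpa is not moved. The rule is stated to serve secondary analysis, and its destination group is named by dTpa.

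**Step 3: direction and size.** Measure mean effects relative to mothers with neither exposure. Let v be the effect of recent dTpa, i of recent infection alone and w of dTpa over 5 years ago. Let fA be the infection-only share of the exposed side and fB the older-dTpa share of the comparator. The plan gives none of these.

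- Observed contrast = (1 − fA)·v + fA·i − fB·w.
- Same contrast without infection-only mothers = v − fB·w, which is what objective 1 asks for.
- Error from infection-only mothers = fA·(i − v).

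The error is zero if i = v, shrinks a positive vaccine effect if i < v, and inflates it if i > v.

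*Infection-only mothers alone* (fB = 0, i = 0): retained share = 1 − fA. Purely as an assumption, let the clean contrast have 80% power at two-sided 5%, with unchanged group sizes and variance. Power is then Φ(retained × (1.960 + 0.842) − 1.960).

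| fA | Retained | Power |
|---|---|---|
| 0% | 100% | 80% |
| 5% | 95% | 76% |
| 10% | 90% | 71% |
| 20% | 80% | 61% |

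With i = 2v and fA = 10%, the contrast is 0.9v + 0.1 × 2v = 1.1v, an inflation of 10%.

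*Both sources, judged against Hypothesis 3 as worded* (i = 0, w = v): retained share = 1 − fA − fB. At 5%/5%, 90% is retained (power 71%); at 10%/10%, 80% (61%); at 20%/20%, 60% (39%). This needs two extreme assumptions at once: no effect of recent infection and an undiminished effect of old vaccine.

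**The case against.** The best defence is that nothing in the protocol says Hypothesis 3 is tested as Stratum A against Stratum B. Section 5.2 defines groups for randomisation. Section 14.1 uses a different term, and section 8.1.2 records both vaccination and infection history, so a dTpa-only factor can be built. Defining it could be left to the SAP, which is not shown. This stands in part. A reader might infer that the maternal question cannot be answered; the documents do not support that. But section 5.3 is not silent. It states a grouping rule for secondary analysis, and that rule, followed as written, gives the wrong membership for its label.

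A reader might also infer that placing mothers vaccinated over 5 years ago in Stratum B undermines objective 1. It does not. Objective 1 asks about receipt within 5 years, so those mothers can properly be comparators. Only the wording of Hypothesis 3 conflicts.

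The combined stratum also has a rationale. Section 2.4.2 is concerned with pre-existing maternal antibody, for which recent infection is a plausible source, and maternal pertussis antibody is measured directly (section 11.1.1). That supports A/B as a randomisation factor. It does not support reporting the split as a dTpa effect.

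Finally, the shares may be small. Section 5.2 accepts infection only when diagnosed by test and confirmed. Section 2.4.2 dates the health-worker dTpa requirement in New South Wales to 2007, and section 2.2.3 describes maternal levels as waning rapidly. These are fair reasons to expect a modest error, and they rule out claiming a definite size.

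**Conclusion.** The point holds in limited form. The only stated rule for grouping mothers in secondary analysis keeps confirmed infection-only mothers on a side labelled by dTpa, against both Hypothesis 3 and objective 1. Separately, the comparator in Hypothesis 3 disagrees with Stratum B and with objective 1.

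The error is fA·(i − v). It could be negligible or serious, and in either direction, because the document gives neither the share of infection-only mothers nor the relative effects of infection and vaccine. The percentages above are illustrations under stated assumptions, not estimates for this trial.

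The consequence is confined to a secondary, non-randomised comparison of mothers. A reader might suspect that the birth-dose comparison is biased too. It is not: a combined stratum is a legitimate randomisation factor, whatever its label.

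**What to change.** - Keep strata A and B for randomisation and as the stratification factor in the birth-dose comparison. Call them strata there, not maternal dTpa status.
- For Hypothesis 3 and objective 1, define maternal dTpa status as verified dTpa within 5 years before delivery against no dTpa in that period. A dose given after delivery does not count. This limit is needed because Table 2 lists a parental dTpa booster at Visit 1 in both groups; section 5.2 already places mothers vaccinated between delivery and enrolment in Stratum B.
- Put mothers with confirmed pertussis within 5 years in a separate level, or exclude them from both sides. Both sides matters: removing them only from the comparator would leave mothers with both exposures among the vaccinated, and the mixing would remain.
- Reword Hypothesis 3 to match objective 1, and correct the group label in section 5.3.
- Add a sensitivity analysis that excludes mothers vaccinated more than 5 years before delivery.

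The cost is wording, using history already collected under section 8.1.2, and slightly fewer infants in one secondary contrast. The randomised comparison does not change.
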